**Exclusion Criteria**:

1. Children with history of acute metabolic decompensation such as DKA within previous 2 months.
2. Children on chronic medications known to affect blood glucose such as systemic corticosteroids.
3. Patients with known poor compliance and HbA1c >12%.
4. Associated co-morbidities like Celiac disease and Hypothyroidism.

**Randomization and allocation concealment:** Participants will be randomized to intervention (Professional CGMS+SMBG) or control (SMBG alone) arms in equal numbers. Randomization will be done using computer generated random number list. Group allocation will be concealed with opaque sealed envelopes.

**Sample Size**: With a 1:1 randomization ratio and based on the assumption of a common SD of 1.5%, an absolute difference of 1% in HbA1c between study groups can be detected with an alpha error of 0.05 (two sided) and a beta error of 0.20, using formula n= 2 x K x SD^2^ /delta ^2^ (where K is constant, SD is standard deviation and delta is magnitude of difference to be detected). Sample size of 34 participants each in the intervention and control group will be required.

**Statistical analysis:**Baseline characteristics will be calculated as means and SD. Results will be presented as means (95% CI).Statistical significance will be set at P<0.05. The primary endpoint will be the unit change in HbA1c over 4 months from intervention. Secondary end points will be percentages of low (<70) and high (>200) sugar records of the total sugar records (SMBG). Continuous variables will be compared using a two-sided *t* test or paired *t* test for change within each subject/group before and after intervention (Professional CGM). Intergroup comparisons of HbA1c will be made using a signed-rank test. Univariate ANOVA will be used to examine factors that may confound the change in HbA1C. Data will be analysed using SPSS (SPSS Inc., Chicago, IL, version 18.0 for Windows).

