**Study Procedures:**

**Intervention group:** All children enrolled in the intervention group will be placed on CGM (*i* Pro 2 Professional CGM™) for 72 hours and finger-prick blood glucose will also be monitored by glucometer (SMBG) at least 4 times per day with proper record of time. CGMS will be placed, on each patient enrolled after written informed consent, by investigator (after proper training) under supervision of the Physician In-charge. These patients will also record their daily activity, meals, snacks and other relevant information with exact time. Record of timing and doses of insulin injections will be maintained. All above information will be recorded on a patient log sheet by caregiver. Information with respect to actual duration and timing of wearing of CGM, any problems occurring in wearing CGM (like proper fitting, local irritation or redness/ pain), reasons for removing CGM if at all, any restriction in daily activities of the child (as told by parents/child) will be recorded,. Patients will continue to do SMBG during and after CGM. CGMS will be removed after 72 hours by the investigator. Report will be prepared using online Therapy Management Software after connecting CGMS with computer. Analysis of Professional CGM report will be done by one of the two Clinicians In-charge of the clinic and further modification in treatment will be advised based on CGM and SMBG records. Also investigations done prior (auto-immune workup, HbA1c, thyroid function test, TTG IgA etc) will be recorded. Mean of atleast 2 previous HbA1c (excluding one at diagnosis) will be recorded, Percentage of Low and high blood sugars recorded over previous 3 months and 3 months post CGM will be recorded. After modification of treatment guided by CGMS and SMBG, these patients will be followed every 2 months (for at least 4 months) with HbA1c levels and SMBG recorded on Diabetic Log book/Diary. Average of HbA1c on 2 occasions post CGM will be recorded. Also percentage of low sugar records seen on SMBG will be noted in follow up.

**Control group**: All other procedures will be same except that, no Professional CGM will be done in this group and treatment advice/modification will be based only on SMBG records.

On each visit patients in both groups will get diabetic education regarding importance of glucose control, insulin dose titration, diet management and exercise etc by same set of clinician and dietician.

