**Parameters before and after intervention (POST-CGMS and SMBG Vs SMBG alone):**

|  | **CGMS+SMBG** | | | **SMBG ALONE** | | |
| --- | --- | --- | --- | --- | --- | --- |
|  | **Base line** | **2 months** | **4 months** | **Base line** | **2 months** | **4 months** |
| **HbA1c** |  |  |  |  |  |  |
| Percentage of low blood sugar |  |  |  |  |  |  |
| Percentage of high blood sugar |  |  |  |  |  |  |
|  |  |  |  |  |  |  |
|  |  |  |  |  |  |  |

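### The tests named for the 4-month HbA1c change cannot use the scheduled 2-month value of a child who lacks the 4-month one; a repeated-measures model would, at little cost

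*Protocol*

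**What the plan says.** The endpoint, in the protocol under Statistical analysis, is: "The primary endpoint will be the unit change in HbA1c over 4 months from intervention". The same paragraph gives the tests. In general, "Continuous variables will be compared using a two-sided *t* test or paired *t* test for change within each subject/group before and after intervention". For HbA1c between arms, "Intergroup comparisons of HbA1c will be made using a signed-rank test". Univariate ANOVA is added to look for factors that may confound the change. No longitudinal model is named.

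Under Study Procedures, children in the intervention group are measured repeatedly: "these patients will be followed every 2 months (for at least 4 months) with HbA1c levels and SMBG recorded on Diabetic Log book/Diary". The control group follows the same schedule: "All other procedures will be same except that, no Professional CGM will be done in this group". The before-and-after table in the patient proforma has baseline, 2-month and 4-month columns for HbA1c in each arm. Study Procedures also has the average of two HbA1c values after CGM recorded, but gives that average no role in the analysis.

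The Sample Size paragraph assumes an SD of 1.5%, a difference of 1%, two-sided alpha 0.05 and beta 0.20, and arrives at 34 per arm. It states no allowance for loss to follow-up.

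**The concern.** A change over 4 months needs a 4-month value. A child seen at baseline and 2 months but not at 4 months has no change score, and no named test can take the 2-month result in its place. The trial therefore schedules a predictor of its primary outcome and names no method that uses it when the outcome is missing.

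Two things are at stake. The first is precision: 34 per arm leaves no margin for lost children. The second is bias. The trial is open label and controls receive no device, so families may react differently to a poor 2-month result in the two arms. If they do, the children with a 4-month value no longer form comparable groups. Adjusting for baseline does not repair that, because the loss depends on something measured after baseline.

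The between-group test needs rewording in any case. A signed-rank test works on paired differences, and children in two randomised arms are not paired.

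**Working it through.** **1. The plan's own figure.** With K = (1.960 + 0.842)² = 7.85, the protocol's formula gives n = 2 × 7.85 × 1.5² / 1² = 35.3, or 36 rounded up. The stated 34 is two lower, close enough to confirm the inputs. With 34 per arm and no loss, power is Φ(1 / (1.5 × √(2/34)) − 1.96) = Φ(0.789) = 78.5% (77.3% by the t distribution).

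**2. What each named method needs.**

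| Method | Needs per child | Can use month 2 if month 4 is missing? |
|---|---|---|
| Two-sided t test on change | one change score | no |
| Paired t test within group | baseline and 4 months | no |
| Signed-rank test | one pair | no, and unsuited to independent arms |
| Univariate ANOVA on change | one change score | no |

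**3. Power, by formula.** The protocol gives neither the loss d nor the correlation ρ between the 2- and 4-month changes. Assume d of 5 to 20%, ρ of 0.5 to 0.9, all loss after month 2, and an SD of 1.5% for the analysed quantity. Complete cases leave m = 34(1 − d) per arm. Using month 2 by likelihood gives an effective n = m / (1 − ρ²d). For d = 15% and ρ = 0.7, m = 28.9 and the effective n is 28.9 / (1 − 0.49 × 0.15) = 31.2.

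| Loss | Power, complete cases | Power with month 2 (ρ 0.5 to 0.9) |
|---|---|---|
| 5% | 76.4% | 76.9 to 78.1% |
| 10% | 74.1% | 75.2 to 77.6% |
| 15% | 71.7% | 73.3 to 77.2% |
| 20% | 69.1% | 71.3 to 76.6% |

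Month 2 alone is worth about 0.5 to 7.5 points here, with no baseline adjustment in either column.

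**4. Power and bias, by simulation.** Assumptions: 34 per arm; SD 1.5% at each visit; true effect −0.6% at 2 months and −1.0% at 4 months; 15% lost after month 2. Visit correlations (0–2, 2–4, 0–4 months) are 0.75, 0.80, 0.70 in set A and 0.60, 0.80, 0.50 in set B. In the unequal-loss case, lost controls are drawn from those with a worse than median 2-month change and loss in the CGM arm is random. Ranges show the spread over separate runs of 4,000 or more simulated trials.

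| | Set A | Set B |
|---|---|---|
| Random loss, power: t test on change | 89% | 70 to 71% |
| – baseline-adjusted complete cases | 93% | 80 to 82% |
| – likelihood with baseline and month 2 | 94% | 84% |
| Unequal loss, estimate (truth −1.0): t test | −0.89 to −0.90 | −0.83 to −0.85 |
| – baseline-adjusted complete cases | −0.92 | −0.88 to −0.89 |
| – likelihood with baseline and month 2 | −0.99 to −1.00 | −0.99 to −1.01 |
| Unequal loss, power: t test | 82% | 56% |
| – baseline-adjusted complete cases | 89% | 71% |
| – likelihood with baseline and month 2 | 94% | 84% |

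Under random loss, baseline adjustment supplies 93 − 89 = 4 of the 5 points gained in set A, and about 10 of 14 in set B. Month 2 adds 1 point in set A and 2 to 4 in set B. Under unequal loss, the t test is off by about 0.10 to 0.17% HbA1c and baseline adjustment still leaves about 0.08 to 0.12%.

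**5. A different loss pattern.** Here there is no true effect, about 15% are lost in one arm only with probability rising with HbA1c, and ρ is 0.5 to 0.9.

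| Loss depends on | Bias, complete cases | Bias with month 2 |
|---|---|---|
| the 2-month value | −0.11 to −0.20% | about 0 |
| the unseen 4-month value | −0.22% | −0.04 to −0.17% |

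The arm that loses its poorly controlled children looks better than it is.

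**The case against.** The strongest objection is that the protocol contains no missing-data rule, no analysis population and no complete-case statement, and such detail commonly sits in an SAP, which is not at hand. That stands as far as it goes: a missing rule is no finding. The point concerns the methods the protocol does name, and exclusion of these children follows from what those tests need.

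Four stronger readings are tempting and not supported.

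- A reader might infer that the plan is a complete-case t test. The t test is named for continuous variables in general, and the sentence on HbA1c between groups names the signed-rank test. The t-test results above stand in for a workable two-sample comparison; they do not describe the stated test.
- A reader might infer that every child will have a 2-month HbA1c and that it is thrown away. The visit is scheduled; a child lost earlier has no such value. The recorded average of two later values also leaves its role open.
- A reader might infer that the 2-month data remove bias whatever the cause. They do so only if loss depends on observed values, as step 5 shows.
- A reader might infer that the trial risks a false claim for CGM. In the unequal-loss scenario with no true effect, the t test rejects somewhat more than 5% of the time, but a run of 20,000 simulated trials put rejections favouring CGM at 1.2% and 0.9%, below the nominal 2.5%, and those favouring control at 4.8% and 5.5%. If the CGM arm lost its poor responders instead, the direction would reverse. The documents give no basis for predicting either.

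It is also fair that most of the power gain comes from baseline adjustment.

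**Conclusion.** The point holds in limited form. As written, a child without a 4-month HbA1c adds nothing to the primary comparison even when the 2-month value is known, and the test named for that comparison is for paired data. Under an assumed 15% loss after month 2, the distinct gain from month 2 is about 1 to 4 points of power beyond baseline adjustment. Its larger value is protection against bias of about 0.1 to 0.2% HbA1c, set against a 1% target, if loss depends on the 2-month result and differs by arm. The rate and pattern of loss and the visit correlations are all assumptions; with little or no loss the issue nearly disappears. This is a cheap improvement and does not show that the trial's result would be wrong.

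**What to change.** In the Statistical analysis paragraph, replace the between-group test for the primary endpoint with a mixed model for repeated measures:

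- Outcome: HbA1c at 2 and 4 months. Terms: arm, visit, arm-by-visit and baseline HbA1c, with unstructured covariance.
- Population: all randomised children with any post-baseline HbA1c.
- Primary estimate: the arm contrast at 4 months with its 95% CI, and no other.
- State that the average of two post-CGM values in Study Procedures is descriptive only.
- Sensitivity analysis: a complete-case two-sample comparison of the 4-month change.

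The cost is one paragraph and a slightly more complex model, with no new visits, blood tests or children. Children lost before month 2 are still not recovered, and bias remains, though smaller, if loss depends on unseen 4-month values.

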**Subjects**:

Children with Type 1 Diabetes attending our Pediatric Diabetes Clinic, between the age group of 2-10 yrs, will be randomized into two groups; Professional CGM plus SMBG (intervention group/Cases) and SMBG alone (control group).

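### The between-arm HbA1c comparison is assigned to a signed-rank test, a paired test that has no pairs to work on in this unmatched two-arm trial

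*Protocol*

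**What the plan says.** Under Subjects, the protocol states that children "will be randomized into two groups; Professional CGM plus SMBG (intervention group/Cases) and SMBG alone (control group"). Randomization and allocation concealment adds "Participants will be randomized to intervention (Professional CGMS+SMBG) or control (SMBG alone) arms in equal numbers" and "Randomization will be done using computer generated random number list". No matching, pairing or crossover is described for this trial.

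The Sample Size paragraph uses the formula for two independent means, "based on the assumption of a common SD of 1.5"%, with a difference of 1%, two-sided alpha 0.05 and beta 0.20, and arrives at 34 per arm.

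Statistical analysis defines the endpoint: "The primary endpoint will be the unit change in HbA1c over 4 months from intervention". On reporting it says "Results will be presented as means (95% CI"). It names a two-sided t test or paired t test for continuous variables, worded as a "test for change within each subject/group before and after intervention (Professional CGM"). The next sentence deals with the arms: "Intergroup comparisons of HbA1c will be made using a signed-rank test".

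**The concern.** The Wilcoxon signed-rank test takes one difference per pair, ranks the absolute differences and compares the positive with the negative rank sums. It suits before-and-after data in the same child, or matched pairs. Neither describes the contrast between CGM plus SMBG and SMBG alone.

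An analyst who follows the sentence has two options:

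- Line up the two arms by some arbitrary order. The p-value then depends on that order, and children are dropped if the arms differ in size.
- Run the test inside each arm. That gives two before-and-after tests and no between-arm comparison.

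The Research Question asks whether HbA1c falls more over 4 months with CGM plus SMBG than with SMBG alone, so the sentence bears on the main result. The trial is also open label, and an unspecified pairing leaves a choice to be made after the data are seen.

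**Working it through.** **1. The plan's own sample size.** Inputs from the Sample Size paragraph: SD = 1.5, delta = 1, two-sided alpha = 0.05, power = 0.80.

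- K = (1.960 + 0.842)² = 7.849
- n = 2 × K × SD² / delta² = 2 × 7.849 × 2.25 / 1 = 35.3, so 36 per arm

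The stated 34 is two below this; it corresponds to K = 34 / (2 × 2.25) = 7.56. At 34 per arm the power is 78.5% by the normal approximation and 77.3% by the t distribution. The gap is small and is not the point here. What matters is that the formula is for two independent groups, so the trial is sized for an unpaired comparison of means.

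**2. Are there pairs?** Allocation is individual, 1:1, from a computer list. Equal allocation gives equal target numbers but does not link any child in one arm to a child in the other. The number of defined between-arm pairs is zero. If the arms ended at, say, 34 and 32, at most 32 pairs could be formed and two children would be discarded.

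**3. How the test behaves if pairs are invented.** Simulation of two independent normal samples, 34 per arm, SD 1.5, true difference 0 or 1, 20,000 runs each:

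| Test | Rejection rate, no difference | Power, difference 1% |
| --- | --- | --- |
| Signed-rank on arbitrary pairs | 4.8% | 74.0% |
| Rank-sum (Mann-Whitney) | 4.7% | 74.9% |
| Unpaired t test | 4.8% | 77.5% |

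The average error rate is sound and the average loss of power is small.

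**4. How much one result depends on row order.** In each of two simulated datasets the values were held fixed and only the pairing was reshuffled, 2,000 times:

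| Dataset | p from independent-groups test | Signed-rank p, lowest to highest | Central range | Median |
| --- | --- | --- | --- | --- |
| A | rank-sum 0.039 | 0.002 to 0.17 | 0.021 to 0.113 (5th to 95th percentile) | 0.057 |
| B | rank-sum 0.032; t test 0.043 | 0.001 to 0.32 | 0.014 to 0.134 (2.5th to 97.5th percentile) | 0.055 |

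In dataset A, 41% of pairings gave p below 0.05 and 59% did not. Dataset A was kept because its rank-sum p lay just under 0.05, and B also lies near that threshold, so both show the problem where it bites hardest.

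**5. How often it would matter.** Averaged over simulated trials at the planned effect (difference 1, SD 1.5, 34 per arm), two random pairings of the same data disagreed on significance in about 9% of trials; a repeat with 10,000 trials gave 9.8%. This figure does not depend on selecting a borderline dataset.

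**6. Does the proposed model keep the endpoint?** Let Y0 be baseline HbA1c and Y4 the 4-month value. If Y4 = a + b·arm + c·Y0, then Y4 − Y0 = a + b·arm + (c − 1)·Y0. The arm effect b is the same for both, so adjusting for baseline leaves the contrast in change over 4 months intact.

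**The case against.** The strongest reply is that a valid test is already in the paragraph. The sentence before the disputed one sets a two-sided t test against a paired t test, and the first could be meant for independent groups. HbA1c change is continuous and the sample size is for two means, so on that reading the fault is a conflict between two sentences. This stands in part. But the qualifier in that sentence refers to change within a subject or group, and the sentence that names HbA1c and the between-arm comparison is the more specific. At best the protocol names two competing tests for its primary variable.

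It can also be said that the faulty sentence mentions HbA1c without saying change or level, so its link to the primary endpoint is inferred. That is true, but the inference is a short one. Or signed-rank may be a slip for rank-sum; the text does not say so, and a slip in this place still has to be corrected.

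Three further points are accepted. Type I error is not inflated. The single-dataset ranges illustrate arbitrariness and are not an effect size for the trial. A rank-test p-value beside a mean and CI is awkward but not an error in itself, and the power cost of a rank-sum test is small.

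Last, a baseline-adjusted model is more than the minimum repair: an unpaired t test or a rank-sum test would also remove the fault. That is so; the reasons for preferring the model are given with the fix.

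**Conclusion.** The concern holds. The protocol assigns a paired test to the comparison of two unmatched, independently randomised groups, on its primary variable. The rule is wrong as written and cannot be carried out as a between-arm test without inventing pairs.

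The harm is an arbitrary and non-reproducible p-value, not a raised false-positive rate. At 34 per arm and the planned effect, the verdict on significance would hang on the pairing in roughly 9% to 10% of trials; near p = 0.05 it can go either way on the same data. These figures assume normal data, the protocol's SD of 1.5% and difference of 1%, and complete, equal arms. The structural error does not rest on any of those assumptions.

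It must be corrected before analysis, because it concerns the main result and the correction is simple.

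**What to change.** Replace the signed-rank sentence with: *The primary between-arm comparison of HbA1c at 4 months is the difference in means with 95% CI from a linear model with arm and baseline HbA1c. A Wilcoxon rank-sum (Mann-Whitney) test of change is the sensitivity analysis.* Remove the signed-rank test from every between-arm comparison, and keep paired tests for within-arm change only.

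The model is preferred because it delivers the mean difference with CI that the paragraph promises, matches a sample size built on means, and preserves the change endpoint.

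State in the same place that baseline and 4-month HbA1c are the single values in those columns of the proforma table of parameters before and after intervention. Study Procedures also records a mean of at least two earlier values and an average of two values after CGM, and the analysis should not be left to choose among them.

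The cost is a short edit to the statistical section. The values are already collected, and no extra patients are needed to make this correction.

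### The HbA1c comparison between arms does not adjust for baseline HbA1c, which is collected in both arms; a prespecified ANCOVA would be more precise and would adjust for chance imbalance in baseline HbA1c

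*Protocol*

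**What the plan says.** Material and Methods, Statistical analysis, states: "The primary endpoint will be the unit change in HbA1c over 4 months from intervention". Continuous variables are to be compared by t test or paired t test, and HbA1c between groups by a signed-rank test. None of these takes a covariate. The only mention of other influences on the outcome is "Univariate ANOVA will be used to examine factors that may confound the change in HbA1C". The factors are not listed, and the sentence is not tied to the treatment comparison.

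Randomisation uses a computer-generated list, with no stratification described. Study Procedures has the mean of at least two earlier HbA1c values recorded, and says control-group procedures are the same apart from CGM. The proforma table "Parameters before and after intervention (POST-CGMS and SMBG Vs SMBG alone" has HbA1c at baseline, 2 months and 4 months for each arm.

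**The concern.** Baseline HbA1c is the obvious covariate for an HbA1c outcome, and it is already collected, yet neither the design nor the analysis uses it. Children with a high starting value tend to fall and those with a low one tend to rise. If the arms differ at baseline by chance, part of the difference in change therefore reflects that gap and not CGM. A change score also carries more variance than a model that estimates the baseline slope.

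The univariate ANOVA does not fill this gap. As written, it relates unnamed factors to change and yields no adjusted treatment effect. The protocol itself states these methods, so this is not a detail merely left to a later analysis plan.

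**Working it through.** **Inputs.** From the Sample Size paragraph: "With a 1:1 randomization ratio"; "based on the assumption of a common SD of 1.5" (per cent); "an absolute difference of 1% in HbA1c between study groups can be detected"; "alpha error of 0.05 (two sided) and a beta error of 0.20"; 34 per arm. The protocol does not say whether 1.5% is the SD of an HbA1c level or of its change, and gives no correlation r between baseline and 4-month HbA1c. Both are treated as assumptions below.

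**The plan's own figure.** n = 2 × K × SD² / delta² with K = 7.85 gives 2 × 7.85 × 2.25 / 1 = 35.3, so 36 per arm against the stated 34. Power at 34 per arm is 78.5% (normal approximation) or 77.3% (noncentral t). The stated figure is close.

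**Formulas.** With the same level SD, σ, at both times:
- SD of change = σ√(2(1 − r))
- ANCOVA residual SD = σ√(1 − r²)
- variance ratio, ANCOVA to change = (1 − r²) / (2(1 − r)) = (1 + r)/2, a saving of (1 − r)/2
- shift in the difference in change, given a baseline gap d = (1 − r) × d, in favour of the arm that starts higher

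**Results if 1.5% is the SD of a level** (34 per arm, difference 1%, t test on change against ANCOVA with 65 df):

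| r | SD of change | ANCOVA SD | Variance saving | 95% CI half-width, change / ANCOVA | Power, change / ANCOVA | Shift for a 0.5% gap |
|---|---|---|---|---|---|---|
| 0.3 | 1.775 | 1.431 | 35% | 0.86 / 0.69 | 63% / 81% | 0.35 |
| 0.5 | 1.500 | 1.299 | 25% | 0.73 / 0.63 | 77% / 88% | 0.25 |
| 0.7 | 1.162 | 1.071 | 15% | 0.56 / 0.52 | 94% / 97% | 0.15 |
| 0.8 | 0.949 | 0.900 | 10% | 0.46 / 0.44 | 99% / 99.5% | 0.10 |

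**Results if 1.5% is the SD of change.** Unadjusted power is 77% whatever r is. ANCOVA power is 92%, 88%, 84% and 81% at r = 0.3, 0.5, 0.7 and 0.8.

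**Size of a chance gap.** With level SD 1.5%, the baseline difference between arms has SE 1.5 × √(2/34) = 0.36, so its 95% range is about ±0.71. A gap of 0.5% is 0.5/0.36 = 1.4 SE.

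**What Table 1 implies about r.** The first trial listed gives 95% CIs for change of −0.7 to −0.1 (19 children) and −0.8 to 0.2 (17 children).
- Half-width 0.3: SD = 0.3/2.10 × √19 = 0.62
- Half-width 0.5: SD = 0.5/2.12 × √17 = 0.97 (approximate, because this interval is not centred on its estimate)

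Setting σ = 1.5 and solving 2(1 − r) × 2.25 = SD²:
- SD 0.62: 1 − r = 0.38/4.5 = 0.09, r about 0.91, saving about 4%
- SD 0.97: 1 − r = 0.94/4.5 = 0.21, r about 0.79, saving about 10%

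The second trial's 0.68 and 0.78, if these are SDs of change, fall between the two. If σ were 1.0% instead (an assumption), the same change SDs would give 1 − r = 0.19 and 0.47, and savings of about 10% and 24%.

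**The case against.** The strongest reply is that this is a matter of efficiency. A reader might infer that the unadjusted comparison is biased or invalid. It is not: under randomisation the comparison of change is unbiased over repeated allocations and keeps its error rate. That part of the reply stands. What remains is lost precision and an error conditional on the gap actually observed.

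Other strong readings also fail:
- **Baseline is strongly prognostic because HbA1c may reach 12%.** The third exclusion criterion joins known poor compliance with HbA1c above 12%, so read literally it sets no ceiling for compliant children. A permitted range would not establish r in any case.
- **A baseline gap of a few tenths is itself as large as the effects in Table 1 (0 to 0.33% between arms).** Only (1 − r) of the gap passes into the difference in change. A 0.3% gap shifts it by 0.15 at r = 0.5 and 0.09 at r = 0.7.
- **Power rises from 77% to 88%.** That holds at r = 0.5. With change SDs of 0.62 to 0.97, as the first trial in Table 1 suggests, unadjusted power for a 1% difference is already at least 98%.
- **Covariates will be picked from the data and put into the efficacy test.** The ANOVA sentence leaves this open but does not say it, nor does it say that the ANOVA follows the main test.
- **ANCOVA removes chance imbalance in general.** It adjusts for imbalance in baseline HbA1c, under a linear model, and not for other factors.

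The use of a signed-rank test for two independent arms is a separate matter and adds no weight here.

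**Conclusion.** The point holds as an almost free improvement to the primary analysis, not as a fault that invalidates it. The protocol fixes a comparison that ignores a covariate it already collects. The variance saving from ANCOVA over the change score is 25% at r = 0.5, 15% at r = 0.7, and 10% or less from r = 0.8. The last range is what Table 1 suggests if 1.5% is a level SD, so the likely gain may be modest. These figures assume equal SDs at the two times and a linear relation. Averaging either the baseline or the follow-up values would change r, and would normally raise it and shrink the gain. Against the planned 1% difference the conditional shift is small to moderate; against between-arm effects of the size in Table 1 it could matter.

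**What to change.** In the Statistical analysis paragraph, state that the primary analysis is a linear model of 4-month HbA1c on arm and baseline HbA1c (continuous), reporting the adjusted mean difference with its 95% CI. Three further points need settling:

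- **Which values are used.** Say whether baseline is the visit value or the mean of earlier values, and whether the outcome is the month-4 value or the average of the two follow-up values. The Statistical analysis paragraph, Study Procedures and the proforma table leave this open.
- **Further covariates.** Fix any other covariate, such as age, in advance, or omit it.
- **The univariate ANOVA.** Label it exploratory, with no role in the efficacy conclusion.

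The cost is a few sentences and one degree of freedom, with no extra visit or blood test.
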